## Abstract

**Background:**

Psychotic disorders are a leading cause of disability in young adults. Antipsychotics have been the primary intervention for psychosis for over 60 years, and yet, we have made little progress in treating negative symptoms, neurocognition, and functional disability. There is growing evidence that cannabidiol (CBD) is effective in treating positive psychotic symptoms, possibly also negative and neurocognitive symptoms, and moreover is well tolerated compared to other psychotropic medications. Anecdotally, patients participating in the Cognitive Assessment and Risk Evaluation (CARE) Early Psychosis Treatment Program at the University of California, San Diego, are self-administering CBD and report subjective improvement in stress, anxiety, and ability to cope with symptoms. The overarching aim of the trial is to explore the effectiveness of CBD augmentation on symptoms and neurocognition in early psychosis while also exploring the mechanism of action of CBD and predictors of response to treatment. The mechanism by which cannabidiol has a therapeutic effect on psychosis is poorly understood. Recent evidence has suggested that CBD may reduce stress and pro-inflammatory biomarker levels. Endocannabinoids also have powerful roles in eating behavior, reward, and mood, indicating these neurotransmitters may play a role in reducing hyperphagia and metabolic abnormalities that are present early in the course of psychotic illness and exacerbated by antipsychotic medication. The neurophysiological effects of CBD have been studied in animal models of psychosis that show improvements in information processing in response to CBD, but there are no studies in individuals with early psychosis.

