### Overall design

The study will be conducted in the UCSD CARE (University of California, San Diego, Cognitive Assessment and Risk Evaluation) Early Psychosis Program where we have a multidisciplinary team of psychiatrists and psychologists with expertise in early psychosis, integrative medicine techniques, biomarkers, and clinical trials. UCSD CARE early psychosis and treatment program is in the Psychiatry Department of the University of California San Diego, California. The CARE early psychosis clinic sees up to 4 new patients per week, generally consisting of a relatively high percentage of patients who would be eligible for this study. The catchment area is the entirety of the multicultural and diverse county of San Diego. The coordinating team is part of UCSD CARE and is comprised of the PI, a clinical psychologist, a graduate student, a clinical research coordinator, and three research associates. The research associates are responsible for identifying potential recruits via outreach and referral screenings, consenting participants, and implementing the test battery. The clinical psychologist and graduate student are responsible for administering the clinical measures. The testing procedures are overseen by the clinical research coordinator who manages the study database and coordinates the study with the outside collaborators. The collaborators on this project are the two funding agencies. The first agency is the Krupp Center of Integrative Research at UCSD co-directed by the statistician consulting on this project. The second agency is the Center for Medicinal Cannabis Research (CMCR) which acts as the IND sponsor, monitors the study progress, provides ongoing assistance to the PI on study design and any issues that arise, and will provide assistance in analyzing the study results. The CMCR will also host the collected data and provide long-term storage for the biological samples collected during the study. The samples will not undergo genetic analysis and will be used only for metabolic and inflammatory analysis and will not be specifically stored for future use.

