### Participants

In order to be eligible to participate in this study, an individual must meet all of the following criteria:Between the ages of 16 and 30.Acceptable diagnoses will include attenuated psychosis syndrome (APS) per the Structured Interview for Prodromal States (SIPS) [79] or first-episode psychosis (onset within the last 2 years) and meet one of the following diagnoses: psychosis NOS, schizophreniform, schizophrenia, and schizoaffective per the Structured Clinical Interview for DSM-V [80].Stabilized on a current treatment regimen for at least 4 weeks prior to initiating the trial consistent with the FDA-NIMH-MATRICS guidelines for clinical trial design for clinical enhancing drugs [81]:Clinically stable and in a nonacute phase of their illness for at least 2 monthsIf currently on antipsychotics, will have been maintained on a current antipsychotic for at least 6 weeks, with no change in antipsychotic dose for the previous 4 weeksExhibit no more than moderate levels of positive symptoms (defined by ratings of ≤ 4) on PANSS items P1 (delusions), P2 (conceptual disorganization), P3 (hallucinatory behavior), P5 (grandiosity), P6 (suspiciousness), and G8 (unusual thought content), but still symptomatic (defined by ratings ≥ 2 on positive symptoms items); no more than a minimal level of depressive symptoms as assessed by the Calgary Depression Scale for Schizophrenia (CDSS) [82]

An individual who meets any of the following criteria will be excluded from participation in this study:Concomitant medical or neurological illnessSignificant head injuryCurrent substance misuseIQ < 80 (below which is considered at least borderline-impaired on Stanford-Binet Fifth Edtion)High suicidal risk assessed by the Columbia-Suicide Severity Rating Scale (C-SSRS) [83]Pregnant women and those who do not agree to avoid becoming pregnantPatients requiring treatment with azelastine, fluticasone, dronabinol, valproic acid, or divalproex sodium

If clinically significant, untreated symptoms are found to be present at baseline, or are found to develop during the course of the study, participants will be advised to consult with their mental health care provider and will also be provided with referrals to UCSD (e.g., UCSD CARE Early Psychosis Specialty Clinic-clinical arm of the CARE) and appropriate clinicians in the community. These participants will continue to be followed in the study, with information on treatment recorded in the database.

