### Treatment

The Epidiolex and matching placebo are manufactured and supplied by Jazz Pharmaceuticals. The Epidiolex formulation is a 100-mg/mL solution. The CBD compound will be dosed at 1000 mg/day administered in two divided doses after an initial 1-week lead-in of 500 mg. The dose of CBD was selected based on previous controlled trials that demonstrate the efficacy of CBD in patients with schizophrenia [16]. The active pharmaceutical ingredient in cannabidiol oral solution is a pharmaceutical-grade synthetic cannabidiol manufactured according to the current good manufacturing practice (cGMP). It is an off-white to pale yellow resin or crystal substance that is soluble in several organic solvents with an acid dissociation constant (pKa) of 9.64. The solution is a clear, colorless to pale yellow to brown colored solution filled into a 30-mL amber glass bottle of 100 mg/mL strength (i.e., 3000 mg per container) that will be stored at a controlled room temperature (20 to 25 °C, 68 to 77 °F) at the study center where the investigational product will be dispensed. DEA regulations are followed and detail specific security requirements for storage of the investigational product in a “securely locked, substantially constructed cabinet.” Investigators must notify the DEA of the theft or significant loss of any controlled substances within 1 business day of discovering such loss or theft. Any loss in investigational products must be reported to the sponsor. The matching placebo is identical in texture, color, taste, and packaging and will be administered in the same volume as the CBD, so that parents, participants, and investigators should not be able to detect differences between the two treatments. Upon reception of the Epidiolex and placebo bottles, they are all relabeled with an identical label and each assigned a unique number by a team member who is not part of the study and who will be the only person with access to the list identifying the numbers with the vial contents.

Adherence will be assessed during a weekly check-in, bottle inspection, and CBD blood levels at the beginning, 3 weeks, and end of the trial. Participants will be queried as to whether they have missed doses of antipsychotic or study medication. Ease of study recruitment and attrition from the study will also be documented.

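### Non-study CBD is not barred although the host programme reports its patients taking it, so the CBD-placebo contrast can be diluted by an unknown amount

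*Protocol article*

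**What the plan says.** - **Background use.** The abstract states that patients in the CARE programme "are self-administering CBD and report subjective improvement in stress, anxiety, and ability to cope with symptoms". It labels this anecdotal and gives no rate, product or dose.
- **Setting.** Overall design begins: "The study will be conducted in the UCSD CARE", so the programme in that remark is also the trial's setting.
- **Exclusions.** Under Participants the list opens with "An individual who meets any of the following criteria will be excluded from participation in this study". It includes a substance misuse item and a medicines item for patients "requiring treatment with azelastine, fluticasone, dronabinol, valproic acid, or divalproex sodium". CBD and cannabis products are not named.
- **Existing treatment.** Participants must be "Stabilized on a current treatment regimen for at least 4 weeks prior to initiating the trial", and study drug is added to that treatment. No washout from non-study CBD, and no bar on it during the trial, is stated.
- **Blood levels.** Under Treatment: "Adherence will be assessed during a weekly check-in, bottle inspection, and CBD blood levels at the beginning, 3 weeks, and end of the trial". The accompanying question to participants concerns missed doses of antipsychotic or study medication. No consequence is given for a positive level at entry or in a placebo participant.
- **Analysis set.** Data analysis keeps every randomised participant with a baseline and at least one post-baseline evaluation.

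**The concern.** The document itself says that the study drug is in use in the clinic that hosts the trial, and then gives a drug-level exclusion list that leaves it out. An item on misuse does not clearly reach ordinary use of a product that the article describes as not psychoactive. A current user therefore satisfies the stated criteria, can be allocated to either arm, may continue, and stays in the analysis.

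Two routes to a smaller observed effect follow:

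- Placebo participants may start or increase CBD after randomisation, which moves the placebo arm towards the active arm.
- Established users in the CBD arm may gain less from added study drug, because part of any response is already in their baseline. Such baselines also feed the planned moderator analyses of baseline symptoms and biomarkers.

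At stake are power and the reading of a small or null difference.

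**Working it through.** **Inputs.** From Data analysis: 120 participants (60 per group), two-tailed 1% level, 80% power, 20% dropout, d = 0.47 and g = 0.39 in absolute value, with the contrast on change from baseline to end of treatment. The affected share q is not in the document; 10%, 20% and 30% are assumed.

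**The plan's own figure.** For two means, n per arm = 2(2.576 + 0.842)² / d².
- d = 0.47: 2 × 11.68 / 0.2209 gives 106; 106 / 0.8 gives 133 per arm, 266 in total.
- g = 0.39: 2 × 11.68 / 0.1521 gives 154; 154 / 0.8 gives 193 per arm, 386 in total.

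So 120 is not reproduced without an unstated gain from baseline adjustment. That is a separate matter. The dilution factor below does not depend on it, and for power I take the claimed 80% at face value.

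**Dilution formula.** Let q1 be the share of established users in each arm whose response is already saturated: they show no further change in either arm. Let q2 be the share of the placebo arm that starts CBD and obtains the full effect.
- Mean effect-related change, CBD arm: d(1 − q1)
- Mean effect-related change, placebo arm: d × q2
- Difference: d(1 − q1 − q2) = d(1 − q), with q = q1 + q2

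With the SD held fixed, required N rises by 1/(1 − q)². If those affected get or lose only half the effect, q is replaced by q/2.

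**Power.** With 48 completers per arm (60 × 0.8), 80% power at 1% corresponds to a standardised signal of 2.576 + 0.842 = 3.418. After dilution, power = Φ(3.418(1 − q) − 2.576), with q/2 in place of q for half effect.

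| Assumed q | d = 0.47 becomes | N factor, full effect | 120 becomes | Power from 80%, full effect | N factor, half effect | Power from 80%, half effect |
|---|---|---|---|---|---|---|
| 10% | 0.423 | 1/0.81 = 1.23 | 149 | 69% | 1/0.9025 = 1.11 | 75% |
| 20% | 0.376 | 1/0.64 = 1.56 | 188 | 56% | 1/0.81 = 1.23 | 69% |
| 30% | 0.329 | 1/0.49 = 2.04 | 245 | 43% | 1/0.7225 = 1.38 | 63% |

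For a given q, the full-effect columns are the upper bound on this dilution.

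**The case against.** **The article condenses a longer protocol.** It cites an IRB protocol at version 17, which is not shown and may bar non-study CBD or define misuse to include it. That is possible. But the article is not silent on eligibility: its list goes down to named medicines and includes one cannabinoid. The point concerns how those stated criteria fit a risk that the article itself raises.

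**Stable users do not bias a change score in the obvious way.** This stands. A steady user on placebo carries any CBD effect in the baseline and adds no further change, and randomisation balances such users on average. Dilution from them arises mainly through a smaller added effect in the CBD arm.

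**Full effect is close to a worst case.** This also stands. The article reports an earlier add-on trial at 600 mg/day with no significant drug-by-time effect on PANSS and no cognitive benefit. Participants also come through community referrals, social media and ResearchMatch, so a remark about clinic patients need not describe trial entrants.

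**Stronger readings that the document does not support.**
- *Placebo participants are on CBD and the effect is diluted.* The document gives no rate, dose or evidence of use within the trial. It supports only that dilution can occur.
- *A null result could not be separated from contamination.* The planned CBD levels at 3 weeks and the end would show CBD in placebo participants. The first level would show prior use if drawn before dosing. Contamination could therefore be partly identified; what is lacking is any stated use of the levels beyond adherence.
- *Power falls from about 38% to 16%.* Those figures for d = 0.47 with 48 per arm start from the separate sample-size discrepancy. The low starting point cannot be attributed to CBD use.

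**Conclusion.** The concern holds as a gap in the stated eligibility criteria and in the stated use of the CBD levels: a current user of the study drug can be randomised, may continue, and is analysed like anyone else. The direction of the risk is towards no difference; its size cannot be known from the document. Under assumed shares of 10% to 30%, the sample-size factor runs from 1.23 to 2.04 at full effect and from 1.11 to 1.38 at half effect. These figures assume a fixed SD and one common degree of effect among those affected. Few users or small amounts would make the loss minor. The change is worth making because it is specific, reduces a foreseeable bias, and relies on samples already planned.

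**What to change.** **Eligibility, for remaining enrolment.** Add current use of non-study CBD or other cannabinoid products to the exclusion criteria. If the full protocol already has such a rule, state it in the published list.

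**During the trial.** Add a question on non-study CBD to the weekly check-ins. Specify that the CBD level planned for the beginning is drawn before the first dose.

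**Analysis, including those already randomised.** Prespecify detectable pre-dose CBD as a covariate and as a sensitivity or subgroup factor. The covariate alone does not recover a lost effect, so the comparison among participants without detectable pre-dose CBD is the informative one. Report the share of placebo participants with detectable CBD at 3 weeks and at the end. Keep these participants in the main analysis, since the later levels are measured after randomisation.

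**Blinding.** Withhold the CBD levels from blinded staff until database lock, because on-study levels can reveal allocation.

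**Cost.** A short amendment, some extra screen failures and a slightly narrower population. The analysis part needs no new samples, provided that the first one is drawn before dosing.

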**Method:**

A total of 120 individuals in the early stages of psychosis will be randomized to 1000 mg of CBD versus placebo as an adjunct to existing treatment in a 8-week, double-blind superiority randomized control trial. The primary outcome measures are symptoms and neurocognition.

**Discussion:**

We hypothesized that CBD will improve symptoms and neurocognition as well as secondary outcome measures of neurohormones, inflammation, eating behaviors, and information processing. Importantly, predictors, moderators, and mediators of the CBD effects will be examined. A better understanding of which individuals are likely to respond to CBD can inform treatment planning and personalize treatment.

**Trial registration:**

ClinicalTrials.gov NCT04411225. Registered on June 2, 2020.

## Introduction

The epidemiological literature demonstrates an association between the early use of cannabis, greater lifetime use, more potent strains, and later risk for psychotic illness [1–4]. Cannabis use during adolescence is now considered a significant environmental factor that is not only associated but might contribute to the development of psychotic disorders [5]. The prefrontal cortex (PFC), with a key role in the pathophysiology of psychosis, continues to develop throughout adolescence and dynamic fluctuations in components of the endocannabinoid (eCB) system also occur throughout adolescent development [6–8]. The critical role of the eCB system in neuronal development and synaptic plasticity [9] suggests that this eCB-controlled regulation relates to the fine-tuning of PFC circuits established during adolescence. Translational studies have revealed the role of eCB receptors and endocannabinoids in dopamine and glutamatergic regulation, both of which are linked to the pathophysiology of schizophrenia [10–13].

Schizophrenia and related psychotic disorders are neurodevelopmental disorders that fully emerge during late adolescence or early adulthood and are a leading cause of morbidity, mortality, and disability. Over the last 2 decades, the scientific focus in psychosis research has shifted to early identification and prevention with the prospect of preventing neuropathological changes and the devastating effects of this disabling illness. Patients who meet the criteria for attenuated psychosis syndrome (APS) have up to a 30% risk of conversion to a full psychotic syndrome within 2 years [14], yet effective pharmacologic interventions, which can disrupt the progression of symptoms, have yet to be identified. Individuals who have already progressed to the early stages of psychosis respond to antipsychotic medication in terms of their positive psychotic symptoms but the negative and neurocognitive symptoms are very difficult to treat, leading to long-term difficulties in social, role, and global functioning and often lifelong disability. In addition, the metabolic abnormalities that often accompany psychotic illness lead to chronic medical issues.

Because cannabidiol (CBD) can reverse many of the biochemical, physiological, and behavioral effects of CB1 receptor agonists such as tetrahydrocannabinol (THC), a handful of studies have explored the possible role of cannabinoids, including CBD, in the treatment of psychosis. There is growing evidence that CBD has the potential to improve positive, negative, and cognitive symptoms of psychosis [15, 16], but the mechanism of action is not well understood and the efficacy of CBD has not been studied in EP when it is likely to have the most robust effect given the greater neuroplasticity in the early stages of illness.

## Previous CBD trials in psychotic illness: symptoms and side effects

There are relatively few studies of CBD alone or as augmentation in psychotic illness. Leweke et al. [17] compared cannabidiol versus amisulpride 200–800 mg per day each in a 4-week double-blind, parallel-group, randomized, active-controlled clinical trial of 42 patients. Treatment with CBD versus the antipsychotic was associated with significantly fewer extrapyramidal symptoms, less weight gain, and lower prolactin increase. CBD was well tolerated and did not affect hepatic or cardiac functions. There was a significant clinical improvement assessed over 28 days as measured by a decrease in the Positive and Negative Syndrome Scale (PANSS) among both amisulpride and CBD groups. In another study, McGuire et al. [16] performed a double-blind, parallel-group trial of adjunctive CBD (1000 mg/day) or placebo that was added to existing antipsychotic treatment in 88 patients with schizophrenia. CBD was well tolerated, and rates of adverse events were similar in the CBD (30 AEs in 15 patients) and placebo group (35 AEs in 16 patients). Patients in the CBD group compared to the placebo group had lower positive psychotic symptoms and were more likely to be clinician-rated as improved and as not severely unwell. Gastrointestinal events (nausea and diarrhea) were the most common in the group taking CBD and were reported as mild, resolving without intervention. Only two events in the CBD group were considered treatment related (dyslipidemia and nausea), and both were considered mild. Boggs et al. [18] performed a 6-week, randomized, placebo-controlled, parallel group, fixed-dose study of CBD (600 mg/day), or placebo augmentation in 36 stable antipsychotic-treated patients with chronic schizophrenia for tolerability of CBD treatment and cognitive effects. Side effects were similar between CBD and placebo except sedation was more prevalent in the CBD group. One participant in the CBD arm withdrew early due to sedation. Approximately 20% of the CBD participants reported mild sedation and 5% in the placebo arm reported sedation. The most common side effects noted were gastrointestinal in nature, but these were more frequent in the placebo arm 10/18 (51%) vs 6/18 (33%) on CBD and not statistically different. There was again an overall significant decrease in PANSS ratings among study subjects without reaching significance for correlation with the CBD group (drug × time interaction), and there was no improvement in cognitive scores in any group [18]. Notably, one open-label pilot study [19] evaluated CBD administration in addition to usual therapy for six patients with diagnoses of Parkinson’s disease and psychosis over 6 months. CBD did not worsen motor function or cause adverse effects, and there was a significant improvement in symptoms per the Brief Psychiatric Rating Scale and Parkinson Psychosis Questionnaire. Adjacent and related to psychosis, a recent trial randomized adults above 60 years of age with major neurocognitive disorder with behavioral disturbances to receive broad-spectrum cannabis oil, and it was found that patients experience a decrease in the Cohen-Mansfield Agitation Inventory score by week 16 [20]. CBD effects in early psychosis patients, where there is the greatest potential for neuroprotection and prevention of deterioration, have yet to be studied.
